
#### Neurophysiological outcomes

2.4.3

We will acquire brain signals before and after the intervention to compare the brain activity. Electroencephalography (EEG) signals will be recorded using a 32-channel g.Nautilus system (g.tec Medical Engineering). The electrodes will be placed according to the extended 10–20 international system. The ground channel will be located on the forehead, and the reference channel will be in the right earlobe. The participants will be seated in a comfortable chair. The session will start with preparing and placing electrodes (lasting approximately 30 min) and will continue with resting-state recordings (20 min). We will instruct all participants not to think about anything. We will acquire brain signals with the participants’ eyes closed and eyes open at rest for 5 min twice (20 min).

Cortical excitability will be measured using transcranial magnetic stimulation (TMS) (MagPro stimulator, MagVenture, Lucernemarken, Denmark) at four time points (T0, T2, T4, and T8). During the measurements, the participants will be seated in a comfortable recliner and will hold their hands on their laps in a supine position. The participants will remain silent during the study to avoid speech-induced modulation of cortical excitability. The participants will also be monitored for drowsiness and will be asked to keep their eyes open throughout the motor-evoked potentials (MEP) measurements. A figure-of-8 coil will be employed to stimulate the motor cortex, orienting the coil handle 45° posterior to the midline to ensure perpendicular electromagnetic current flow to the central sulcus (29). The coil will be moved over the scalp in 1-cm increments. For the electromyographic (EMG) signal recording, an active surface electrode will be attached to the contralateral first dorsal interosseous muscle, while reference and ground electrodes will be placed on the index finger’s proximal interphalangeal joint and over the wrist, respectively. Relaxation of the measured muscles will be controlled by continuous visual EMG monitoring. EMG signals will be captured in terms of amplitude and frequency. The “hot spot,” identified as the scalp location yielding the largest MEP amplitude with the lowest stimulation intensity, will be determined (30).

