### Statistical methods

2.11

A repeated-measures analysis of variance at the time level (T0, T2, T4, and T8) will be applied to examine whether primary, secondary, and neurophysiology outcomes improved after the intervention. Paired t-tests will be used as post-hoc tests to examine significant changes in different combinations of time points for the scores. The normality of the data will be checked using Kolmogorov–Smirnov tests, and the results will show whether the data are normally distributed. The Bonferroni correction will be used for multiple comparisons.

The Friedman test will be performed for within-group comparisons between time points for non-normally distributed data. The Wilcoxon signed-rank test will also be used for within-group comparisons at each point in time. The resting-state EEG data (with eyes closed) will be first preprocessed to analyze the changes in functional connectivity in the motor area before and after the intervention. The raw EEG data will first be filtered using a 3rd-order Butterworth filter with 1 and 50 Hz cutoff frequencies. Subsequently, it will be divided into 1-s epochs without overlaps. Epochs showing large artifacts, detected using a signal threshold of ±120 μV, will be removed. Next, 30 artifact-free epochs will be randomly chosen for each participant. Partial directed coherence (PDC), a representative effective functional connectivity measure, will be used to evaluate changes in directed functional connectivity from the premotor area to the motor area before and after the intervention (15, 33). Based on the previous study (15), two frequency bands, μ (10–12 Hz) and β (18–24 Hz) bands, will be used for the calculation of PDC. The PDC values will be normalized to a range of 0–1 and then averaged across each participant. Ten consecutive MEPs will be recorded for each stimulus intensity to measure the changes in corticomotor function. These measurements will determine each subject’s average ICI and ICF responses by calculating the mean of 10 trials of paired-pulse TMS. Statistical analyses will be performed using SPSS 21.0 (IBM SPSS Statistics, NY, United States), with the significance level set at *p* < 0.05.

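### Computing EEG connectivity from 30 randomly chosen one-second epochs uses about 5% of the eyes-closed recording and adds avoidable, draw-dependent noise to a non-primary outcome

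*Protocol article*

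**What the plan says.** Section 2.4.3 (Neurophysiological outcomes) describes the resting recording: "We will acquire brain signals with the participants’ eyes closed and eyes open at rest for 5 min twice (20 min" in total. Section 2.11 (Statistical methods) then restricts the connectivity analysis to one condition: "The resting-state EEG data (with eyes closed) will be first preprocessed to analyze the changes in functional connectivity in the motor area". The signal is filtered and "divided into 1-s epochs without overlaps". Cleaning follows: "Epochs showing large artifacts, detected using a signal threshold of ±120 μV, will be removed". From what remains, "30 artifact-free epochs will be randomly chosen for each participant". PDC in the μ and β bands is computed from these epochs and "will be used to evaluate changes in directed functional connectivity from the premotor area to the motor area before and after the intervention".

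Table 1 lists EEG at T0, T2, T4 and T8, and section 2.11 covers the neurophysiological outcomes with its general model: "A repeated-measures analysis of variance at the time level (T0, T2, T4, and T8) will be applied". The article gives no reason for the number 30 and mentions no repeated draws or averaging over draws.

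**The concern.** The epoch count and the random selection are stated rules, not details left open. When a recording holds several hundred clean epochs, keeping 30 at random has two effects. The PDC estimate for that visit is less precise than the recording allows. The value also depends on which 30 epochs were picked, so two analysts with the same files and different seeds would get different PDC values and possibly different p-values.

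This happens at every visit, so the noise enters twice in any change score. The trial has 20 patients per arm and no power calculation (section 2.5), and brain activity is part of its stated aim, so it has little room for noise that costs nothing to remove.

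**Working it through.** **Recording length.** Two conditions × 5 min × 2 repeats = 20 min, which reproduces the total in section 2.4.3. The eyes-closed share is 2 × 5 min = 600 s, or at most 600 non-overlapping 1-s epochs per visit.

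**Fraction used.** 30/600 = 5.0% of the recorded eyes-closed data. The protocol gives no expected rejection rate, so a range is assumed:

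| Assumed rejection | Clean epochs m | 30/m | SE ratio √(m/30) | Share of 30-epoch sampling variance due to the draw, 1 − 30/m |
|---|---|---|---|---|
| 0% | 600 | 5.0% | 4.47 | 95% |
| 50% | 300 | 10.0% | 3.16 | 90% |
| 70% | 180 | 16.7% | 2.45 | 83% |

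The last two columns treat epochs as independent and PDC as behaving like a mean over epochs. The 30 epochs are read as per participant per visit. Read literally as per participant over four visits, the fraction would be 30/2400 = 1.25%.

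**Effect on a comparison of change (illustration).** Set the variance of true change to 1 and let k be the epoch SD divided by the SD of true change. The protocol does not give k. With m epochs per visit and two visits in a change score:

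- variance of observed change = 1 + 2k²/m
- standardised effect = 0.91/√(1 + 2k²/m), where 0.91 gives 80% power without epoch noise (20 per arm, two-sample t test, two-sided 5%)
- SD of the t statistic from the draw alone, with N clean epochs available = √[(2k²/30)(1 − 30/N) / (1 + 2k²/30)]

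| k | Variance, 30 epochs | Power, 30 epochs | Variance, 300 epochs | Power, 300 epochs | SD of t from the draw, N = 600 |
|---|---|---|---|---|---|
| 0.5 | 1.017 | 79% | 1.002 | 80% | 0.12 |
| 1 | 1.067 | 77% | 1.007 | 80% | 0.24 |
| 2 | 1.267 | 70% | 1.027 | 79% | 0.45 |
| 3 | 1.600 | 60% | 1.060 | 78% | 0.60 |

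For example, at k = 2 the variance with 30 epochs is 1 + 2 × 4/30 = 1.267, and the draw SD is √[(0.267 × 0.95)/1.267] = 0.45.

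**Check on actual PDC.** PDC is a nonlinear, model-based estimate, so redrawing was also tried on one synthetic recording (six channels, with an assumed 250 Hz sampling rate and autoregressive order 5; 400 redraws of 30 from 600 epochs). The draw moved PDC by an SD of about 0.016–0.021. That is a coefficient of variation of about 2–7% for true links and about 53% for a link with no true connection. The null link averaged 0.038 with 30 epochs and 0.0065 with all 600, so short data also pushes weak links upward.

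**The case against.** The strongest reply is that an equal amount of data per recording is sound practice, because the bias of PDC depends on data length, and a fixed 30 ensures it. This stands as an argument for equal counts, although the article does not make it. It does not support so low a count or a single draw.

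The second reply is that the loss may be trivial, and this largely stands. At k = 0.5 or 1 it is 1 to 3 percentage points of power. The illustration also leans towards a larger loss:

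- It leaves out other visit-to-visit noise, such as cap placement or vigilance. If that noise equals the true-change variance, the 30-to-300 variance ratio at k = 3 falls from 1.51 (1.600/1.060) to 1.26 (2.600/2.060).
- It treats adjacent epochs as independent. With an assumed lag-1 correlation of 0.2 to 0.6, the SE ratio at 600 epochs is about 3.7 to 2.4 instead of 4.5.
- It uses a between-arm t test of change, whereas the tests named in section 2.11 run over time. The 80% benchmark is also an assumption, because this pilot has no power calculation.

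A reader might infer that PDC is the trial's main measure of brain activity. The protocol does not say so: section 2.4.3 lists EEG beside motor threshold, MEP amplitude and intracortical inhibition and facilitation, without ranking them. A reader might also infer that the draw could favour one arm. It cannot, because the selection is random within each recording.

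**Conclusion.** The point holds as a matter of efficiency and reproducibility. The stated rule uses 5% of the recorded eyes-closed data and makes a non-primary outcome depend on a random draw. The 5% and the dependence on the draw follow from the text, reading the sentence as one draw per visit.

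The cost in power does not follow from the text. It runs from about 1 point (k = 0.5) to about 20 points (k = 3), assuming independent epochs, no other visit-to-visit noise and a two-sample comparison of change. The documents therefore do not support a claim that the EEG analysis is badly underpowered because of this rule. Nor do they support any claim of bias between arms or of a threat to the primary outcome. The change is worth making because it costs almost nothing.

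**What to change.** In section 2.11, replace the sentence on choosing 30 epochs with wording such as: *For each participant and each time point, PDC will be computed from the same number of artifact-free epochs.* Then state:

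- the number, well above 30, set before unblinding from the clean-epoch counts alone;
- a rule for recordings that fall short, so that the worst recording does not set the count for all;
- that where a recording has more clean epochs than the common number, PDC is averaged over many random draws of that size with a fixed seed.

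If the common count cannot be raised, averaging PDC over many draws of 30 is the fallback. It is not equivalent: it removes the dependence on the draw but keeps the short-data bias.

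The cost is some computing time and the need to agree a rule for poor recordings. No new data are needed and there is no burden on patients.

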## Discussion

3

Several systematic reviews on BCI have reported clinical and functional improvements and neurophysiological changes (5, 6, 34). These findings indicate that the proposed intervention method promotes optimal functional reorganization during the recovery process of the affected limb. However, it is essential to verify each BCI system, especially the working of MI-contingent feedback, because the communication of MI and neurofeedback is a core feature of BCI. The present study aims to verify the MI-contingent feedback of a commercially available BCI system, RecoveriX PRO. Considering the lack of commercially available BCI rehabilitation systems for patients with stroke, this verification could be helpful for real clinical settings. Additionally, there is a shortage of studies, which have verified this MI-contingent BCI system in patients in the subacute phase of stroke. Therefore, this study may accelerate the use of a BCI system in general stroke rehabilitation settings, not only limited to a research setting.

The strengths of our study include the intention to recruit a larger sample size than that of previous studies, particularly focusing on patients in the subacute stage of stroke. In addition, we aim to enhance the interpretation of the outcome measures by employing a diverse set of evaluation tools. Our study seeks to incorporate a variety of assessments, including EEG and MEP, that have not been comprehensively utilized in prior investigations. This approach will allow for a more comprehensive evaluation of neuroplasticity from the cerebral cortex to the end-effector. Furthermore, our study aims to measure the extent of BCI experience, motivation, and quality of life through subjective questionnaires. Overall, we believe that these data will serve as a foundation for demonstrating the comprehensive impact of BCI.

However, an expected limitation of this study is the potential occurrence of fatigue and tiredness because of the daily sessions conducted five times a week for 1 h each. This type of fatigue is commonly observed in BCI studies. If participants report feeling fatigued or finding the task challenging, we will proceed only after ensuring that they take sufficient rest. In addition, therapists will consistently motivate the patient throughout the process. Further, after each run, they will display the results provided by the RecoveriX PRO to encourage and maximize the patients’ motivation. Unlike traditional BCIs, our study employs a virtual reality-based game task. We believe that the game will enhance motor performance, as BCI participation is facilitated by motivation and active engagement (35). Moreover, feedback provided by the game plays a crucial role in sustaining patient concentration (36). Another issue is the sample size, which may not be sufficient to fully capture the variability in the population, potentially limiting the generalizability of the findings. However, compared to previous studies, our sample size cannot be considered small. We will recruit 20 patients per arm. Therefore, should be able to minimize the likelihood of these limitations.

The protocol used in this study can serve as a foundation for future basic research in the clinical setting of BCI interventions. Furthermore, it aims to stimulate the advancement of foundational research on MI-contingent feedback for BCI interventions in the subacute stroke domains. If these aspects are successful, BCI may play an important role in stroke rehabilitation in the future.

## Conclusion

4

We hypothesize that contingency between MI-related neural correlates and rich sensory feedback is essential in closed-loop BCI systems for functional improvement and neural plasticity. Therefore, we aim to investigate whether differences in function and neural plasticity arise from the close contingent connection between MI-induced brain activity and the consequent feedback. We will compare the effects of the BCI system operated by MI-contingent feedback (real-BCI) versus MI-independent feedback (sham-BCI) on distal upper limb function and brain activity in patients with subacute stroke.

## Ethics and dissemination

5

On the consent form, participants are asked whether they agree to the use of their information for research. The researchers will ensure that they will protect the confidentiality of all personal information obtained during this study and that the form they sign will ensure this. When disclosing personal information obtained from this research to a journal or conference, their names and other personal details will not be included. However, personal information may be provided if required by law. In addition, monitors, inspection personnel, and the National Rehabilitation Center Clinical Trial Review Board may directly view or submit research-related data to verify the reliability of the research procedure and data within the scope of the relevant regulations without infringing on the confidentiality of the research participants. By signing this agreement, the patient will be deemed to have knowledge of its contents and agree to comply with it. The results of this research will be published in academic journals and journal papers, and the institution’s reports will also be published.
